#### Secondary analysis

The association between CSF profiles and the occurrence of any new spinal cord lesion within two years (binary outcome) will be evaluated using a multivariable logistic regression model with intrathecal IgM synthesis (standardized to z-scores using Reiber formula) as the primary predictor. Prespecified covariates are intrathecal IgG synthesis, presence of oligoclonal bands and kappa free light chains. Continuous predictors will be assessed for linearity in the logit and transformed or modelled with splines if needed, multicollinearity will be evaluated using variance inflation factors. Results will be reported as odds ratios with 95% CI. Model discrimination will be quantified by the area under the ROC curve. Distributions of lymphocyte subsets, soluble blood- and blood biomarkers, and clinical variables will be compared between groups with and without new SC-MRI activity, overall MRI activity, and NEDA status using independent *t*-tests or Mann–Whitney *U* tests for continuous variables and χ² tests for categorical variables. Exploratory analyses will compare other baseline characteristics (e.g., center of inclusion, disease duration, treatment choice) across lesion-based subgroups.

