### Statistics

#### Sample size

To estimate the incidence of asymptomatic cord lesions in absence of brain MRI activity, an approximate sample size of 139 will be needed, given an estimated proportion of asymptomatic cord lesions of 10% based on retrospective literature [6, 8, 20] (precision 0.05, confidence level 0.95).

CSF profiles are studied as a priori selected predictor and additionally we provide descriptive data and analyse associations in an exploratory fashion for the other different clinical, radiological, biochemical factors and treatments used in patients with/without new spinal cord lesions, to be able to identify important prognostic candidates, which in turn can be specifically studied in a possible future extension of the study.

Not all collected parameters are included in a prognostic model for spinal cord disease activity, because for the prognostic model to include a wide variety of predictors, a very large population is needed (estimated > 400), which currently is not feasible.

To assess a logistic regression model in which certain CSF profiles (primarily the degree of intrathecal IgM production) are associated with any new spinal cord lesion within two years of follow-up, an estimated sample size of 144 patients is needed to be able to detect an odds ratio of 2 (expected R-squared between main predictor variable and other covariates estimated 0.07 based on retrospective data) with a power of 80%, alpha of 0.05 given that the base expected proportion of patients with new cord lesions within two years is about 15%. The latter figure is based on retrospective data from a local database, where we found that 19% of patients (*n* = 217) developed new cord lesions (regardless of treatment) within 2 years of initiation of a new treatment [11]. In the international MSBase registry this figure was 12% for treatment-naïve RRMS patients starting a DMT (*n* = 528) [12].

Given the calculated sample sizes and an expected loss-to-follow-up of about 2–7% based on other longitudinal prospective MS MRI studies [9, 10], for this study we will aim to include 155 patients.

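### With about 21.6 expected events for four CSF terms, the AUC as written is biased upward; an optimism-corrected AUC should be the reported discrimination result

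*Protocol article*

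**What the plan says.** The protocol article, Secondary analysis, relates any new spinal cord lesion within two years (yes or no) to intrathecal IgM synthesis as main predictor. Three covariates are fixed in advance: IgG synthesis, presence of oligoclonal bands (OCB) and kappa free light chains. That makes at least four parameters. On functional form it says: "Continuous predictors will be assessed for linearity in the logit and transformed or modelled with splines if needed". Odds ratios with 95% intervals are to be reported, and then: "Model discrimination will be quantified by the area under the ROC curve". No internal validation or optimism correction is mentioned.

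The Sample size section sizes this model for the IgM odds ratio: "an estimated sample size of 144 patients is needed to be able to detect an odds ratio of 2", "with a power of 80%, alpha of 0.05", with "expected R-squared between main predictor variable and other covariates estimated 0.07 based on retrospective data". It assumes that "the base expected proportion of patients with new cord lesions within two years is about 15" per cent. This rests on two sources. In a local database, 19% of 217 patients "developed new cord lesions (regardless of treatment) within 2 years of initiation of a new treatment". The second is given as: "In the international MSBase registry this figure was 12% for treatment-naïve RRMS patients starting a DMT" (n = 528). The caption of Fig. 2 makes CSF data conditional on a lumbar puncture having been part of the diagnostic workup.

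**The concern.** An AUC computed on the patients who supplied the coefficients rewards the model for fitting chance patterns. The fewer the events per parameter, the larger the reward, and choosing a transformation or spline from the same data adds to it. The sample size was set to detect one odds ratio; nothing in it concerns the accuracy of an AUC.

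The AUC is the only measure in the Secondary analysis of how well CSF separates patients who develop cord lesions from those who do not. The Perspectives section says prognostic factors are studied to find subgroups that would benefit from regular cord imaging. An inflated AUC would overstate how well CSF could serve that aim.

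**Working it through.** **The plan's own figures.** Inputs from Sample size: odds ratio 2, so β = ln 2 = 0.6931 and β² = 0.4805; event proportion 0.15; R² = 0.07; power 80%; alpha 0.05, taken as two-sided because the side is not stated.
- Closed formula for a continuous, standardised predictor: (1.96 + 0.8416)² / (0.15 × 0.85 × 0.4805) = 128.1. Dividing by 1 − 0.07 gives 137.8, so 138.
- Wald formula with variance correction and a 15% overall event rate: 135.9 / 0.93 = 146.1, so 147, within 3% of the stated 144.
- Enrolment: 144 / (1 − 0.07) = 154.8, so 155, as stated.

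The sample size is therefore reproduced closely enough and is not in dispute.

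**Events per parameter.**

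| Event rate | Events in 144 | Per term, 4 terms |
|---|---|---|
| 12% (registry) | 17.3 | 4.3 |
| 15% (planning value) | 21.6 | 5.4 |
| 19% (local database) | 27.4 | 6.8 |

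Three-knot splines on the three continuous markers give 7 terms, and 21.6 / 7 = 3.1 events per term.

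**Apparent AUC when nothing predicts (true AUC 0.50).** Simulated data: 144 patients, 21 events, maximum-likelihood logistic fit. Assumptions: normal markers with pairwise correlation 0.26 (0.6 gives the same result); 90% OCB-positive, independent of the other markers.

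| Model | Mean apparent AUC | Above 0.60 | Above 0.70 |
|---|---|---|---|
| Four linear terms | 0.62 | 67% | 6% |
| 4-knot spline on IgM only | 0.65 | – | – |
| 3-knot splines on all three markers | 0.67 | 92% | 25% |

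For the linear model, the 5th to 95th percentiles run from about 0.55 to 0.70. The mean is 0.64 with 17 events and 0.61 with 27. If CSF were available in only 110 patients with 16 events (an assumption; the share is not given), it is 0.64. An ordinary 95% interval for the AUC lies wholly above 0.5 in about 43% of null data sets (linear) and 68% (4-knot spline on IgM), against a nominal 2.5%.

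In the spline rows the spline is always fitted. Splines used only when the linearity check calls for them should give a mean between the linear and spline rows.

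**With a real IgM effect, and after correction.** Four linear terms, 144 patients, events drawn at random (about 21.5 to 21.9 on average), 400 data sets, 60 bootstrap resamples each:

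| True IgM odds ratio | Apparent AUC | AUC in new patients | Bootstrap-corrected AUC |
|---|---|---|---|
| 1 | 0.63 | 0.50 | 0.54 |
| 2 | 0.72 | 0.66 | 0.66 |

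A second simulation of the odds-ratio-2 case gives 0.71 apparent against 0.65 true. Under the null the correction leaves about 0.04 of an excess of about 0.13; under an odds ratio of 2 it leaves essentially none.

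**OCB term.** With 21 events and no true association, the chance that no event falls among OCB-negative patients is (OCB-positive share)^21. This gives 0.01 at 80%, 0.03 at 85%, 0.11 at 90%, 0.34 at 95% and 0.65 at 98%. The documents give no OCB prevalence.

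**The case against.** The strongest reply is that this is a journal article. It does not say that the AUC will be left uncorrected, and bootstrap validation is the kind of detail an analysis plan may hold. That stands as far as it goes: a reader might infer that the investigators have decided on an uncorrected AUC, and the documents do not show it. What they do show is a stated measure, a stated data-driven choice of form and an event count from their own assumptions. Followed literally, these give a biased figure.

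The model is also mainly about association. The IgM odds ratio is primary, odds ratios with intervals will stand beside the AUC, no risk score or threshold is planned, and the Sample size section already holds back a wider prognostic model because it would need more than 400 patients. This limits the harm. It does not remove the bias in a figure the plan undertakes to report.

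Three stronger readings are tempting and are not supported:
- A reader might infer that the AUC is bound to suggest discrimination when there is none. For the linear model, 33% of null data sets stay at or below 0.60, and about 57% have an ordinary interval that does not lie wholly above 0.5.
- A reader might infer that the model will break down with an infinite OCB odds ratio. That depends on a prevalence the documents do not give, the risk runs from about 1% to 65%, and it concerns a covariate, not IgM.
- A reader might infer that splines should be banned or penalised fitting required. Checking linearity and using splines where needed is ordinary practice, and either restriction would be a preference.

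**Conclusion.** The point holds in limited form. As written, the AUC of the CSF model is biased upward: by about 0.12 when nothing predicts with four linear terms (0.62 against 0.50), by about 0.15 to 0.17 with splines, and by about 0.06 if the IgM odds ratio is 2. These sizes rest on the protocol's 144 patients and 15% event rate and on the simulation assumptions given with the check. The bias is somewhat larger at the 12% rate or with incomplete CSF, and somewhat smaller at 19%.

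It affects one summary statistic of a secondary analysis. The incidence and number-needed-to-scan analyses are untouched. Separation on the OCB term is a conditional risk and not an error in the plan.

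**What to change.** In Secondary analysis, name the bootstrap optimism-corrected AUC as the discrimination result and show the apparent AUC beside it. State that any transformation or spline selection is repeated within each bootstrap sample, so that the correction also covers the choice of form. If the full protocol or analysis plan already says this, a clause in the article is enough.

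Optionally, name penalised likelihood as a fallback should separation occur on the OCB term.

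The cost is a few lines of analysis code and a less favourable AUC. No extra patients or data are needed, and with data collection due to end in mid-2028 the change can be made before analysis.

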## Perspectives

Despite significant advancements in the management of MS in recent years, the disease remains one of the leading causes of non-traumatic disability in (young-) adults worldwide. There is a pressing need for prognostic markers to better predict disease progression and guide therapeutic interventions. Spinal cord lesions play a critical role in the trajectory of MS and contribute substantially to long-term disability accumulation. However, there are still a lot of uncertainties in regard to follow-up imaging of the spinal cord, which is the core subject of our research. Spinal cord imaging is costly and time-consuming; therefore, it is not efficient to simply add this to the existing brain imaging follow-up protocol. To that end, we are assessing prognostic factors for future spinal cord lesions such as clinical, cerebrospinal fluid and blood biomarkers to identify subgroups of patients that would benefit from regular spinal cord imaging in follow up.

Currently, our knowledge is limited regarding (i) the determinants of spinal cord involvement, (ii) which patients would benefit from more extensive spinal cord MRI follow-up and (iii) how we should treat patients with a greater degree of cord disease activity (the latter knowledge gap falls outside the scope of the present study but could give first insights and provide basis for further research).

Retrospective research provides evidence for the importance of asymptomatic spinal cord lesions on the disease course in MS patients, as well as possible spinal cord disease-prone subgroups. However, prospective research is lacking. The design of this study aspires a better understanding of asymptomatic spinal cord involvement in MS patients and insight into spinal cord-disease prone subgroups of MS patients.

With this study, the goal is to:

Improve understanding of the incidence of asymptomatic spinal cord lesions, particularly how often they occur without accompanying progression on brain MRI.Improve spinal cord imaging monitoring strategies by gathering data on the relevance of these lesions. This includes identifying markers of subgroups prone to spinal cord involvement, which may warrant more tailored monitoring protocols.Support the optimization of personalised monitoring approaches and in turn enhanced personalised treatment approaches, with the ultimate aim of reducing disease progression. Improved monitoring can enhance clinical decision-making and potentially have a meaningful impact on patients’ lives, including their level of disability, psychological well-being, and social participation.

Furthermore, this topic should be the focus of future research, as it has been largely underrepresented in current prospective scientific discourse. At present, there is a significant knowledge gap within this area, and this study seeks to address part of this uncertainty by shedding light on its implications for both patient monitoring, care and future investigations.

The findings are expected to give a renewed insight into the incidence of asymptomatic spinal cord lesions, and the importance of follow-up MRI of the spinal cord in (a subpopulation of) MS patients.

## Data Availability

With the publication of the results, we aim to publish the dataset in a scientific data repository compliant with the FAIR data principles.

## Abbreviations

9HPT: 9-Hole Peg Test
ABR: General Assessment and Registration form (ABR form), the application form that is required for submission to the accredited Ethics Committee; in Dutch: Algemeen Beoordelings- & Registratieformulier (ABR-formulier)
CA: Competent Authority
CCMO: Central Committee on Research Involving Human Subjects; in Dutch: Centrale Commissie Mensgebonden Onderzoek
CIS: Clinically Isolated Syndrome
CSF: Cerebrospinal Fluid
EDSS: Expanded Disability Status Scale
IC: Informed Consent
MRI: Magnetic Resonance Imaging
sICP: soluble immune checkpoint markers
T25-FW: Timed 25 Foot Walking Test
